### Study procedures

Patients undergo assessment of the NIHSS at baseline, 24 h, and 5–7 days (or discharge if earlier), which is a routine clinical procedure. It will be carried out by NIHSS-certified physicians. All patients will undergo NCCT, CTA and CT perfusion or MRI and MRA of the brain at baseline, as part of routine clinical care. CT-perfusion will be focused on the anterior circulation or posterior circulation depending on the suspected location of the ischemic stroke as determined by the treating physician. For follow-up imaging, all patients will undergo an MRI of the brain at 24 h (range: 12 to 48 h). The MRI scan will include the following sequences: [1] Susceptibility weighted imaging (SWI), [2] DWI/apparent diffusion coefficient (ADC), [3] dynamic susceptibility contrast MRI (DSC-MRI) or arterial spin labeling (ASL), [4] T2 weighted imaging (T2w), [5] T2-FLAIR. In case of any contra-indication for MRI after randomization (e.g., because the contra-indication was not known at the time of inclusion or the patient has a new contra-indication due to an intervention during hospital admission), a follow-up NCCT and CT-perfusion at 24 h will be performed instead. Blood samples will be taken at baseline, one tube EDTA (+/− 5 mL), one tube without anticoagulant (+/− 7mL) and two tubes with citrated blood (2.7 mL) will be drawn. Additional blood samples will be taken (two tubes citrated blood of 2.7 mL) at 1 h, at 3 h, and at 24 h post treatment. Biomaterials will only be collected for patients in two participating centers. Plasma samples will be stored at −80 °C for later analysis. A schedule of all activities is shown in Fig. 2.

### Informed consent

This study uses a deferred informed consent procedure, because DUMAS evaluates an acute intervention in an emergency situation concerning a life-threatening disorder [19]. Consent will be asked as early as possible, and as deemed appropriate according to the treating physician.

If a patient or his/her representative refuses to provide consent, participation in the trial will be terminated immediately. The procedure requires that all information on patients who did not provide consent is discarded and deleted. This may be against the interest of patients who did provide consent, and against the interest of the general public, as patients with (serious) adverse events might be more likely to refuse consent for participation. Not considering these records might very well result in an underestimation of the true safety and validity of the data, and it might lead to undetected safety concerns for all consenting patients in the trial. To overcome this concern, all randomized patients will be registered in an anonymized safety registry providing information on in-hospital symptomatic ICH and in-hospital mortality (both important safety variables for the study). All other information will be completely erased from the patient’s study record in case no consent is provided.

When a patient has died before consent has been obtained, their representative will be informed about trial participation. These patients will be included in all analyses, there is no opt-out option since that may bias study results.

### Study outcomes

The primary outcome is any post-intervention ICH confirmed by neuroimaging according to the Heidelberg Bleeding Classification at 24 h (range: 12 to 48 h) after study drug administration preferably by MRI (SWI) [20]. Secondary clinical outcomes are the NIHSS score at 24 h, the NIHSS score 5–7 days (or discharge if earlier), and the mRS at 30 days [21, 22]. Secondary imaging outcomes are change (pre-treatment vs. post-treatment) in abnormal perfusion volume and infarct volume at 24 h post-treatment. Secondary blood biomarker outcomes include fibrinogen, plasminogen, alpha2-antiplasmine, and d-dimers at 1 h, at 3 h, and at 24 h. Safety outcomes include symptomatic ICH according to the Heidelberg Bleeding Classification, death from any cause within 30 days, and major extracranial hemorrhage according to the ISTH criteria within 24 h of thrombolytic treatment [20, 23].

### (Serious) adverse event reporting

Safety is an issue of concern as thrombolytic treatment has a bleeding risk. Adverse events are defined as any undesirable experience occurring to a subject during the study, whether or not considered related to the investigational product. All adverse events reported spontaneously by the subject or observed by the investigator or his staff will be recorded. A serious adverse event is any untoward medical occurrence or effect that results in death, is life-threatening (at the time of the event), requires hospitalization or prolongation of existing inpatients’ hospitalization, results in persistent or significant disability or incapacity, is a congenital anomaly or birth defect, that required medical or surgical intervention, or any other important medical event that did not result in any of the outcomes listed above due to medical or surgical intervention but could have been based upon appropriate medical judgment. We will report SAEs that occurred within the follow-up period defined by the last follow-up contact.

### Data Safety Monitoring Board

The Data Safety Monitoring Board (DSMB) consists of a neurologist (chair), a neuro-radiologist, and a hematologist. An independent statistician will combine clinical and outcome data in order to report to the DSMB. The DSMB will advise the chairman of the steering committee if, in their view, the randomized comparisons have provided both (i) “proof beyond reasonable doubt” that for all, or some, the treatment is clearly indicated or clearly contra-indicated and (ii) evidence that might reasonably be expected to materially influence future patient management. Appropriate criteria of proof beyond reasonable doubt cannot be specified precisely, but the DMSB will work on the principle that a difference of at least 3 standard errors in an interim analysis of a major outcome event (e.g., any ICH, death) may be needed to justify halting, or modifying a study before the planned completed recruitment. Safety interim analyses will also include measures of efficacy (NIHSS and mRS) and are planned after the inclusion of 20, 30, 40, and 50 patients and after that with increments of 50, after the start of the trial, and after any dose change, until the trial is completed, unless the DSMB advises otherwise during the conduct of the trial. Following a report from the DMSB, the steering committee will decide whether to modify entry to the study (or seek extra data) and inform the sponsor. Unless this happens, however, the steering committee, the collaborators, and central administrative staff will remain ignorant of these analyses and results.

Apart from these safety and efficacy reports, the DSMB will receive additional analyses from an independent statistician, who will inform the DSMB on the likelihood of success or failure of the study to reach a positive result. This information will be used to advise the steering committee to adapt the dosing in the study according to pre-specified criteria as explained in detail in Supplemental File 1. The information provided in these interim analyses will not be used to discontinue the study for expected futility, as it is the intention of the steering committee to run the trial until 200 patients with a final diagnosis of ischemic stroke have been included, as long as there are no safety or efficacy concerns.

### Data collection and management

All data will be entered into a web-based trial management system (OpenClinica), which allows for edit and audit trails, by trained local research personnel. Patient records are coded by a unique study number. The local investigators will keep a list showing codes and names. Unique documents with identifying information will be stored separately from the study database in digital files, categorized by study number on a secure drive system, and only accessible to the study coordinators.

This trial qualifies as a moderate risk study, i.e., a study with a small risk of serious adverse events compared to standard treatment. According to Dutch standards, 25% of local data should be reviewed against source data. However, as this is a phase 2 trial, we will monitor a pre-specified list of local data, which includes secondary outcomes (i.e., the NIHSS at 24 h, the NIHSS at 5–7 days, and the mRS at 30 days), in 100% of the patients.

### Statistical analyses

Baseline data by treatment allocation will be reported with standard statistical procedures and missing values will be reported. For regression analyses, missing values, except the primary outcome, will be imputed using multiple imputation (*n*=5). We will perform and report 4 analyses, of which the first is the primary:Simple modified intention-to-treat analysis to assess overall safety and efficacy. This is a modified intention-to-treat analysis because we exclude patients who did not give consent to participate in the study. We will additionally report safety parameters based on the full cohort, including patients who did not give consent.Targeted modified intention-to-treat analysis excluding patients with a final diagnosis other than ischemic stroke to assess safety and efficacy in the target population.Targeted modified on-treatment analysis to assess the safety and efficacy in patients who actually received treatment excluding patients with a final diagnosis other than ischemic stroke.Per-protocol analysis.

Additionally, we will perform subgroup analyses on categorized baseline variables including age, sex, systolic blood pressure, ASPECTS, time from onset to study treatment, NIHSS score, extracranial carotid or vertebral arterial occlusion, pre-study antiplatelet treatment, DWI lesion (yes/no), and lacunar syndrome (yes/no). Subgroup analyses will be done by testing for interaction of the subgroup indicator with treatment.

The effect of the study treatment on the primary outcome will be assessed with multivariable logistic regression with study treatment as a binary independent variable (m-proUK vs. control). Adjusted and unadjusted effect estimates with corresponding 95% confidence interval (CI) will be reported. The effect estimate will be adjusted for important prognostic factors at baseline, which include at least age and time from onset of symptoms to randomization. Stroke severity (NIHSS score), lacunar syndrome (yes/no) [11], systolic blood pressure, antiplatelet treatment, and endovascular treatment (yes/no) will be considered additionally in this order. Whether the dosing (initial vs. modified) of the study treatment modifies the treatment effect, will be analyzed with a multiplicative interaction parameter in the main analysis.

The effect of the study treatment on the secondary outcomes will be assessed with multivariable linear, logistic, or ordinal regression models with study treatment as a binary independent variable (m-proUK vs. control). The effect parameter will be either a beta or (common) OR with 95% CI. This effect will be adjusted with variables that are predictive of the specific outcome measure.

The most up-to-date statistical analysis plan can be found on the website (https://dumas-trial.nl/).

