### Sample size

We will include 200 patients with a final diagnosis of ischemic stroke randomized 1:1 to either standard thrombolytic treatment or dual thrombolytic treatment. We assume that the primary outcome, any ICH, will occur with a probability of 20% with standard thrombolytic treatment and a probability of 7% in the patients treated with dual thrombolytic therapy [24]. This leads to an overall effect (odds ratio (OR)) of 0.3. This sample size will provide us with a power of at least 77% to detect a statistically significant effect on the primary outcome. This estimate does not take into account the use of multivariable adjustment for differences in baseline characteristics in the primary analysis.

To ensure sufficient power in the targeted modified on-treatment analysis, an additional patient will be randomized and included (i.e., replaced) for each patient whodid not give consent for participation in the study, orfor any reason did not receive the full dose of thrombolytics as assigned, orhad a final diagnosis other than ischemic stroke (i.e., stroke mimic).◦ We estimate that up to 20% of the included patients will not have a final diagnosis of ischemic stroke [25].

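### Subgroup interactions are tested on categorized age, systolic blood pressure, ASPECTS, onset-to-treatment time and NIHSS; if the treatment effect changes gradually with these, a median split loses about a third of the interaction information

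*Protocol article*

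**What the plan says.** In the protocol article, the section Statistical analyses announces additional subgroup analyses: "we will perform subgroup analyses on categorized baseline variables including age, sex, systolic blood pressure, ASPECTS, time from onset to study treatment, NIHSS score". The list goes on to extracranial arterial occlusion, earlier antiplatelet use, DWI lesion and lacunar syndrome. The test follows: "Subgroup analyses will be done by testing for interaction of the subgroup indicator with treatment". The categories are therefore the basis of the test and not only a way to display results. The article mentions no interaction test on the original scale, and it does not say to which outcomes the subgroup tests apply.

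In the same section, the covariates of the primary model are given without any mention of categories: "which include at least age and time from onset of symptoms to randomization", with NIHSS and systolic blood pressure among the further candidates. Lacunar syndrome and endovascular treatment are marked there as yes/no.

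The number of categories and the cut-points are not given. They may stand in the separate analysis plan to which the article refers, and their absence is not part of this point.

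**The concern.** Age, systolic blood pressure and onset-to-treatment time are continuous; ASPECTS and NIHSS are ordinal scores. A test on an indicator treats all patients within a category as alike. If the treatment effect changes steadily with the modifier, the variation within categories carries information on that change, and the test discards it. The article gives no reason for categorizing these variables as effect modifiers.

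At stake is the chance of detecting a real gradient, for example a treatment effect that weakens with stroke severity, in a trial whose interaction tests start with little information.

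**Working it through.** **1. Inputs.** From Sample size: "We will include 200 patients with a final diagnosis of ischemic stroke randomized 1:1 to either standard thrombolytic treatment or dual thrombolytic treatment". The event rates assumed there for the primary outcome are given as "will occur with a probability of 20% with standard thrombolytic treatment and a probability of 7% in the patients treated with dual thrombolytic therapy". Expected events: 100 × 0.20 + 100 × 0.07 = 27. The significance level is not stated; I assume two-sided 0.05, in line with the 95% intervals. The size of any interaction and the shape of the modifiers are assumptions throughout.

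**2. The plan's own figures.** OR = (0.07/0.93)/(0.20/0.80) = 0.301, as stated. For power, the pooled proportion is 0.135. The null SE is √(2 × 0.135 × 0.865/100) = 0.0483 and the alternative SE is √((0.16 + 0.0651)/100) = 0.0474. Then (0.13 − 1.96 × 0.0483)/0.0474 = 0.744, so power is 77.1%. The stated power of at least 77% is reproduced.

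**3. Information kept by categorizing.** For a linear interaction, this is the between-category variance of the modifier divided by its total variance. For a normal modifier split at the median, the category means are ±√(2/π) SD, so the share kept is 2/π = 0.637 and the loss is 36%.

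| Grouping (normal modifier) | Loss |
|---|---|
| Median split | 36% |
| 30/70 split | 42% |
| 20/80 split | 51% |
| 10/90 split | 66% |
| Tertiles | 21% |
| Quartiles | 14% |
| Quintiles | 10% |

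A uniform modifier split at the median loses 25%. An assumed skewed integer score resembling NIHSS lost 37% to 49% under the cuts tried. An assumed score resembling ASPECTS, with most patients at the ceiling, lost 33% to 37% with two groups and 8% with three.

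**4. From information to power.** Suppose the linear test has 80% power. Its noncentrality is (1.960 + 0.842)² = 7.85. A median split leaves 7.85 × 0.637 = 5.00, and power is Φ(√5.00 − 1.96) = 61%. Tertiles (2 df) give 60%, quartiles (3 df) 57% and a 20/80 split 50%. With the extra degrees of freedom counted, tertiles and quartiles are equivalent to losing about 37% and 41% of the sample. Finer grouping therefore keeps more information but does not recover the power.

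**5. Any ICH.** Simulated logistic likelihood-ratio tests with n = 200, rates of 20% and 7%, a normal modifier with a linear interaction, and 1,500 trials per scenario where the number is recorded (Monte Carlo error about 1 point). Where a cell has two figures, two separate runs were made.

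| Interaction (log-odds per SD) | Main effect per SD | Continuous | Median split | Tertiles |
|---|---|---|---|---|
| 0.2 | 0.3 | 7% | 8% | – |
| 0.3 | 0.3 | 11% | 10% | – |
| 0.5 | 0.3 | 18% | 16% | – |
| 0.7 | 0.3 | 27%, 29% | 23%, 23% | – |
| 0.7 | 0 | 35% | 24% | 23% |
| 0.7 | 0.4 | 28% | 23% | 18% |
| −0.7 | 0.4 | 30% | 22% | 22% |
| 1.0 | 0.3 | 48% | 35% | – |
| 1.0 | 0 | 53% | 40% | 37% |
| 1.0 | 0.4 | 46% | 30% | 26% |
| −1.0 | 0.4 | 57% | 41% | 42% |

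A separate simulation (2,000 trials, no main effect, the 7% rate holding at the modifier's mean) gave 42%, 29% and 30% at 0.8 per SD. A skewed integer modifier resembling NIHSS gave 42% against 28% at 0.7. With no interaction, the continuous test rejected in 5–6% of trials, the median split in 6–7% and tertiles in 7–8%, which slightly flatters the categorized tests.

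**6. A continuous secondary outcome.** With an interaction of g residual SD per SD of modifier, the noncentrality is g²n/4. At g = 0.30 it is 0.09 × 200/4 = 4.50, so power is 56%. A median split leaves 4.50 × 0.637 = 2.87, so power is 40%. The gain is 17 points before rounding. A simulation at the same g gave 55% against 35%, a gain of 20 points.

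**7. The reverse case.** If the effect is a step exactly at the cut, the indicator test does better. With a log-OR step of 1.4 at the median, two runs gave 12% and 14% for the continuous test against 25% and 28% for the split. With a step of 2.0 the figures were 19% and 36%.

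**The case against.** Four objections carry weight.

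- **The third is conditional.** A reader might infer that the tests as planned lose a third of their information. The article does not support that, because it fixes neither the number of groups nor the cuts, and the figure also needs a roughly normal modifier and a gradual effect. This stands, and the loss has to be given as a range.
- **The interactions that show a visible gain for any ICH are large.** At 0.7 to 1.0 log-odds per SD, the treatment OR changes by a factor of exp(1.4) = 4 to exp(2.0) = 7 between one SD below and one SD above the mean. At more modest values either test usually misses the interaction. This stands for any ICH; it carries less force for continuous outcomes, where the gain is clear at 0.3 SD per SD.
- **Categories are not without benefit.** A reader might infer that categorizing can only do harm. The step scenario shows otherwise. It is the most favourable case for the indicator test, with the cut exactly at the true threshold, and the article claims no such threshold. Still, the choice exchanges one assumption for another.
- **A normal modifier is a poor model for bounded or skewed scores.** This is fair as a caution, but the assumed NIHSS-like and ASPECTS-like distributions gave losses of similar size for two groups.

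The possibility that the unseen analysis plan sets sensible cut-points does not answer the point. The article itself commits to a test on the indicator, and no choice of cuts restores the power of the linear test when the effect is gradual.

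**Conclusion.** The point holds as a low-severity improvement to the analysis. The stated rule tests five continuous or ordinal modifiers on a coarser scale than they are measured on. Under a gradual effect, the power cost is about that of a median split even with tertiles or quartiles, and greater with unbalanced two-group cuts. The gain from changing the rule is negligible to moderate for any ICH and larger for continuous secondary outcomes. All these sizes rest on assumed interactions, since the article gives none.

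The consequence is limited. These are additional analyses, and the primary effect estimate is not touched. A reader might also infer that weaker subgroup tests would misdirect the choice of a phase 3 population. The article does not support that: its Discussion ties the move to phase 3 to the effect on any ICH, or to a large effect that is consistent over secondary outcomes and fits the pathophysiology and experimental studies. It does not tie that move to subgroup tests.

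**What to change.** Replace the subgroup rule in the analysis plan with:

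> For age, systolic blood pressure, ASPECTS, time from onset to study treatment and NIHSS, effect modification will be tested by the interaction of treatment with the variable on its original scale (linear, with a check for non-linearity). Category-specific estimates will be shown for description only.

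Keep the indicator test for the binary variables: sex, extracranial occlusion, antiplatelet treatment, DWI lesion and lacunar syndrome.

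The cost is one sentence and no new data. Recruitment closed in April 2022, but only the analysis changes, so the amendment can still be made if outcomes by arm have not been analysed. The downside is that the 1-df test assumes an approximately linear interaction. The non-linearity check and the descriptive category estimates let readers judge that assumption.

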**Fig. 2 Fig2:**
[figure not shown]
SPIRIT figure. mRS indicates modified Rankin scale; NIHSS, National Institutes of Health Stroke Scale; SAE, serious adverse events. *t_−1_: directly before randomization, t_0_: randomization, t_1_ = directly after randomization; t_2_ = at 1 h; t_3_ = at 3 h; t_4_ = at 24 h; t_5_ = at 5–7 days or at discharge if earlier; t_6_ = at 30 days. **Informed consent: as early as deemed possible after IV thrombolysis. ***Administration of IV thrombolytic therapy directly after randomization. ****Neuro-imaging at baseline consists of non-contrast CT, CT-perfusion, and CT-angiography or brain MRI and MRA. Neuro-imaging at 24 h consists preferably of a brain MRI

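### DWI lesion is tested as a baseline subgroup, but patients imaged by CT at baseline have DWI only from the post-treatment MRI

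*Protocol article*

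**What the plan says.** All places are in the Protocol article.

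- **Subgroup list (Statistical analyses).** "we will perform subgroup analyses on categorized baseline variables including age, sex, systolic blood pressure, ASPECTS, time from onset to study treatment". The list continues with "pre-study antiplatelet treatment, DWI lesion (yes/no), and lacunar syndrome (yes/no".
- **Test (Statistical analyses).** "Subgroup analyses will be done by testing for interaction of the subgroup indicator with treatment".
- **Missing data (Statistical analyses).** For regression analyses, every missing value other than the primary outcome is to be multiply imputed, with five imputations.
- **Baseline imaging (Study procedures).** "All patients will undergo NCCT, CTA and CT perfusion or MRI and MRA of the brain at baseline, as part of routine clinical care". The legend of Fig. 2 agrees: "Neuro-imaging at baseline consists of non-contrast CT, CT-perfusion, and CT-angiography or brain MRI and MRA".
- **Follow-up imaging (Study procedures).** "For follow-up imaging, all patients will undergo an MRI of the brain at 24 h (range: 12 to 48 h". Its listed sequences include "2] DWI/apparent diffusion coefficient (ADC". A patient found after randomisation to have a contraindication to MRI gets CT instead.
- **Time variables (Statistical analyses).** The subgroup list uses onset to study treatment. The adjustment covariates are those "which include at least age and time from onset of symptoms to randomization".

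**The concern.** A subgroup interaction can be read as effect modification only if the subgroup is fixed before treatment. The plan labels DWI lesion a baseline variable, but its imaging schedule does not supply that variable at baseline for patients who go through CT.

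If the gap is filled from the follow-up MRI, patients are sorted by something treatment may have changed. If one regimen reperfuses better, some of its patients who would have shown a lesion will not, and they move into the DWI-negative group in that arm only. The arms are then no longer comparable within either stratum, and an interaction can appear where the true effect is constant. If the gap is filled by imputation, the test rests partly on modelled values for a measurement that was never planned for those patients.

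What is at stake is the reading of one secondary interaction test. The primary comparison does not depend on it.

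**Working it through.** **1. The plan's own figure.** The only related figure is the power of at least 77% in Sample size. Inputs from that section are 200 patients randomised 1:1 (100 per arm) and ICH risks of 20% and 7%. A two-sided 5% level is assumed, since the article does not state one.

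- Pooled risk = (0.20 + 0.07)/2 = 0.135
- SE under the null = √(2 × 0.135 × 0.865/100) = 0.0483
- SE under the alternative = √(0.20 × 0.80/100 + 0.07 × 0.93/100) = 0.0474
- Power = Φ[(0.13 − 1.96 × 0.0483)/0.0474] = 77.1%

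The figure reproduces, and nothing below changes it. Expected ICH events are 100 × 0.20 + 100 × 0.07 = 27.

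**2. When DWI is available.**

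| Group | DWI before treatment | DWI after treatment |
|---|---|---|
| CT at baseline | None | 24 h MRI (12 to 48 h) |
| MRI at baseline | Obtainable; needed for the DWI-FLAIR route in Patient population | 24 h MRI |

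The article does not give the split between the two rows. DWI is a listed sequence only for the follow-up scan. The one place that ties a DWI lesion to a time point is Study organization, where the absence of a lesion on the follow-up scan triggers discussion of a possible mimic.

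**3. Two readings for CT-route patients.**

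- *Follow-up DWI is used.* The stratifier is measured after treatment, on the scan that preferably yields the primary outcome (Study outcomes). The same section makes infarct volume at 24 h a secondary outcome, so the plan itself allows that treatment may change tissue injury by then.
- *Baseline DWI is meant.* The value is missing by design for each of these patients. The imputation rule as written would fill it in, and no restriction to MRI-route patients is stated.

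**4. Illustration of the first reading.** Only the planning odds ratio comes from the documents: (0.07/0.93)/(0.20/0.80) = 0.301. The rest is assumed:

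- the true odds ratio is 0.301 in every patient group;
- 80% would be DWI-positive at 24 h under control;
- control ICH risk is 24% in lasting DWI-positive and 4% in DWI-negative patients (0.80 × 0.24 + 0.20 × 0.04 = 0.20, the planning rate);
- dual therapy turns a share r of all patients (switchers) DWI-negative.

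Worked case: r = 5%, switchers' control ICH risk 10%.

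- Applying the odds ratio, treated risks are 24% → 8.68%, 10% → 3.24%, 4% → 1.24%.
- DWI-positive: control risk (0.75 × 0.24 + 0.05 × 0.10)/0.80 = 23.1%; treated 8.68%; odds ratio 0.316.
- DWI-negative: control risk 4%; treated (0.20 × 0.0124 + 0.05 × 0.0324)/0.25 = 1.64%; odds ratio 0.400.
- Spurious ratio of odds ratios (negative over positive): 0.400/0.316, which is 1.26 from unrounded values.

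| r | Ratio, switchers' risk 10% | Ratio, switchers' risk 24% |
|---|---|---|
| 0% | 1.00 | 1.00 |
| 2% | 1.13 | 1.56 |
| 5% | 1.26 | 2.24 |
| 10% | 1.40 | 3.08 |

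The correct ratio is 1.00 in every cell.

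**The case against.** **The label already settles it.** The plan calls these baseline variables, so on a literal reading only pre-treatment DWI counts. The mention of follow-up DWI in Study organization concerns adjudication of mimics and does not define the subgroup. The choice of scan could also be left to the analysis plan. This stands in part: a reader might infer that follow-up DWI will be used, and the article does not say so. It does not remove the problem, because the literal reading meets the imputation rule, which has no exception for a measurement that CT-route patients never had.

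**Most or all patients lack baseline DWI.** A reader might infer this, but the article gives no CT/MRI split, and the DWI-FLAIR route shows that some patients do have it. The text supports only that every patient imaged by CT alone at baseline lacks it.

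**Onset-to-treatment time is also affected by treatment.** A reader might infer this because that interval ends after randomisation in an open-label trial. The documents do not support it. Thrombolysis is given directly after randomisation (Fig. 2 legend), the interval ends before any drug can act, both arms start with an alteplase bolus (Study treatment), and no difference in preparation time is reported. What remains is a mismatch with the adjustment covariate.

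**The size is assumed and the test is weak anyway.** Both are true. With about 27 expected events any interaction test is imprecise, and the phase 3 criteria in the Discussion do not mention subgroups. This limits the importance of the point but does not make the test valid.

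**Conclusion.** The point holds for DWI lesion. For patients imaged by CT at baseline, the planned interaction test either conditions on a variable that treatment can affect or relies on imputed values.

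Its size cannot be taken from the documents. In the illustration the spurious ratio of odds ratios runs from 1.00 to 3.08, according to the assumed share of switchers and their ICH risk. It is 1.00 if treatment changes no one's DWI status by 24 h. The number of patients concerned equals the unreported number on the CT route.

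For onset-to-treatment time only a minor inconsistency stands. The matter is confined to additional subgroup analyses and is worth correcting because the correction is cheap.

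**What to change.** 1. State which scan defines DWI lesion. Preferably, restrict this subgroup to patients with a baseline MRI, and state that the variable is not imputed for the others.
2. If follow-up DWI is used instead, move it out of the baseline list, label it a post-randomisation descriptive analysis, and do not interpret it as effect modification.
3. For consistency, define the time subgroup as onset to randomisation, which is already an adjustment covariate.

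Substituting a perfusion deficit on baseline CT perfusion is not a clean alternative. CT perfusion belongs to the CT route, so it could be missing for MRI-route patients.

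The cost is one or two lines in the analysis plan and a smaller, less precise DWI subgroup. No new data are needed, and the primary analysis and the stated power stay as they are.
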